### Data collection

Data collection will take place at baseline (T0), after the courses finish (T1) and 12 weeks after completing the courses (T3) (see figure 1). Additionally, a brief questionnaire will be sent to the participants each workday. Data collected at T1 will be considered as the primary end-point of interest.

**Figure 1 F1:**
[figure not shown]
Study procedures and timeline. Items in bold denote data collection.

### Outcomes

#### Feasibility, acceptability, and procedural outcomes

To determine feasibility of a later-stage trial, we will examine descriptive statistics to:

Estimate between-condition effect sizes:For the primary outcome, to inform a power calculation for a later-stage trial.For the cognitive control outcomes, to determine suitability of these measures to index mechanisms of interest.Determine feasibility of running a later-stage trial by monitoring recruitment (the percentage of employees who consent into the study), retention, including timing of measurements (by indexing percentage of participants completing each time point), and potential contamination issues, most notably, measuring the extent to which participants talked about their course with participants from the other arm.Acceptability of interventions by indexing which course the participants would have preferred to be randomised to, their regularity in engaging in exercise and mindfulness, and intervention dose, notably the percentage of course materials attempted.Procedural uncertainties, for example, by exploring the suitability of our primary measure in indexing our primary outcome. To this end, we have introduced several work-related outcomes (see Secondary Outcomes).Potential covariates influencing key outcomes which may need to be considered in design of the later-stage trial, including:Participant mental and physical health at baseline.Importance of job to participants’ identity at baseline.

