### Study design

This is a participant-level RCT. Employees will be randomly allocated in a 1:1 ratio to either of two parallel groups.

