### Sample size

One of the procedural uncertainties limiting the design of a fully powered trial is the size of the effect on the main outcome in interest. As a traditional power calculation is unfeasible given the lack of previous data, we seek to determine the likely effect size in this study, to inform a later-phase trial.

We aim to recruit 240 participants. A fully online design may cause a high loss to follow-up; a systematic review of internet-based RCTs found the average attrition rate to be 47% at postintervention.^76^ Based on this, we have selected a sample size which we anticipate will yield complete data for 128 participants at our primary end-point of postintervention (64 per arm) and 68 participants at follow-up (34 per arm). In clinical research with lower attrition rates, feasibility trials tend to recruit 36 participants.^77^ Considering high risk of attrition and the considerable uncertainties regarding the feasibility of the trial, we estimate that our sample size is optimal to examine the feasibility of procedures and provide a reliable estimate of effect size.

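### The between-arm effect size is the only stated basis for judging whether the cognitive tasks suit the mechanism, and alone it cannot tell an insensitive task from a course that does not change cognitive control

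*Protocol article*

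**What the plan says.** The section Feasibility, acceptability, and procedural outcomes lists what descriptive statistics will be used for. The first item is "Estimate between-condition effect sizes", with two purposes. For the primary outcome the purpose is to plan the later trial. For the tasks it is this: "For the cognitive control outcomes, to determine suitability of these measures to index mechanisms of interest". The article sets no size of effect that would count as suitable and names no other criterion for the tasks.

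The section Cognitive control mechanisms describes an emotional stop-signal task, with response time in stop-trials as its main outcome, and an affective reversal learning task, with the proportion of correct responses as its main outcome. It gives no reliability or validity figure for either.

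The Sample size section expects "complete data for 128 participants at our primary end-point of postintervention (64 per arm) and 68 participants at follow-up (34 per arm").

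**The concern.** Choosing mechanism measures for the definitive trial is one of the stated purposes of this study. A between-arm difference shows a task's sensitivity only if the course is already known to move what the task measures. Here that is the hypothesis. The Objectives section sets out to explore whether improved cognitive control is a mechanism. The Introduction reports a small average effect on cognitive control overall and, for emotional stimuli, a single null study that it calls likely underpowered.

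A task could therefore look unsuitable because the course does nothing to cognitive control, or look suitable through sampling error. There is also some circularity: preferring tasks that showed a difference favours the mechanism they are meant to test.

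The article treats its primary measure differently. For the work functioning questionnaire it cites internal consistency, test-retest reliability and convergent validity, and it plans to examine suitability by means of several other work-related outcomes. The tasks have less stated support and a weaker stated test.

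**Working it through.** **Inputs from the protocol article**
- Recruitment (Sample size): "We aim to recruit 240 participants".
- Allocation (Study design): 1:1.
- Attrition (Sample size): "a systematic review of internet-based RCTs found the average attrition rate to be 47% at postintervention".
- Effect on cognitive control (Background and rationale): overall g = 0.2, not specific to these tasks.
- Analysis of other outcomes (Statistical methods): the same regression as for the primary outcome, so adjusted for baseline and employer.

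**Assumed, because the article does not give them:** g = 0.2 applies to these tasks; SD = 1; baseline-to-outcome correlation r of 0 to 0.7; task reliability of 0.5 for the first illustration.

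**1. The plan's own numbers.** 240 × (1 - 0.47) = 127.2, stated as 128. Applying the same rate again, 128 × 0.53 = 67.8, stated as 68. Both reproduce. The article states no power figure to check.

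**2. Confounding.** Measurement error shrinks a standardised difference: observed d = true d × √reliability. A true effect of 0.20 on a task of reliability 0.5 gives 0.20 × √0.5 = 0.14. A true effect of 0.14 on a perfectly reliable task gives the same 0.14. An observed zero can mean no course effect or a task that does not register one. Sample size does not enter, so a larger trial would not resolve it.

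**3. Precision.** SE = √(2/n) × √(1 - r²), with n per arm. The interval is 0.2 ± 1.96 × SE. The chance of an estimate at or below zero is Φ(-0.2/SE), with signs set so that positive favours mindfulness.

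| n per arm | r | SE | 95% interval around 0.2 | Estimate ≤ 0 |
|---|---|---|---|---|
| 64 | 0 | 0.177 | -0.15 to 0.55 | 12.9% |
| 64 | 0.5 | 0.153 | -0.10 to 0.50 | 9.6% |
| 64 | 0.7 | 0.126 | -0.05 to 0.45 | 5.7% |
| 34 | 0 | 0.243 | -0.28 to 0.68 | 20.5% |

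The half-width at 64 per arm without adjustment is 1.96 × 0.177 = 0.35 whatever the true effect. If the true observable effect were 0.14, the chance of an estimate at or below zero would be Φ(-0.141/0.177) = Φ(-0.80), about 21%; at no effect it is 50% by symmetry.

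**4. Do other parts of the plan separate the two explanations?** The decentring and mindfulness questionnaires (Mindfulness-related outcomes) check whether the course raised mindfulness, not whether it changed cognitive control. The mediation analysis (Statistical methods) uses the task scores as given and is not tied to judging the tasks. Neither removes the ambiguity in step 2.

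**The case against.** The best defence is that suitability here means suitability to index a mechanism, and a candidate mediator has to respond differently in the two arms. Light exercise was chosen because only mindfulness is expected to improve cognitive control, so the between-arm difference is the design's natural measure of responsiveness. Reliability coefficients cannot supply that. This stands: the effect size is relevant and should be kept. It is insufficient rather than irrelevant, because a lack of response has two explanations.

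Two stronger readings are tempting and are not supported. A reader might infer that the plan contains a rule that would regularly discard sound tasks and keep unsound ones. It does not: the effect sizes are described as descriptive, with no cut-off and no keep-or-drop decision, so no discard rate follows.

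A reader might also infer that the criterion barely beats chance. For telling an effect of 0.2 from none, a cut at 0.1 is right Φ(0.1/0.177) = 71% of the time at 64 per arm (66% at 34 per arm), and 74% to 79% at 64 per arm with baseline adjustment at r of 0.5 to 0.7. Figures near chance, 52% to 60% at 64 per arm without adjustment, arise only for a narrower comparison: a perfectly reliable task against one of assumed reliability 0.8 to 0.3, when the course works and the cut lies midway. None of these cuts is in the article.

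The article also says openly that it is not powered and that estimation is the aim. That answers a complaint about power, but not one about what the estimate is used to decide. Finally, psychometric detail is often left to an analysis plan that is not shown here. Its absence would be no finding; the point is that the article names a criterion and that the criterion is inadequate alone.

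**Conclusion.** The point holds in a limited form. The only basis the article states for judging the tasks mixes measurement quality with course efficacy, and a small or null difference is uninterpretable on that question at any sample size. That conclusion needs no numerical assumption.

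The imprecision is secondary. It rests on applying g = 0.2 to two affective tasks for which the article has almost no prior evidence, and on an assumed baseline correlation. The unadjusted interval at the primary end-point covers both no effect and a moderate one; the planned baseline adjustment narrows it but, over the range assumed, still leaves zero inside.

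The primary outcome and its analysis are unaffected. What is at stake is one feasibility decision, the choice of mechanism measures for the later trial.

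**What to change.** In Feasibility, acceptability, and procedural outcomes, or in the analysis plan if the article cannot be changed, separate the two uses. Report the between-arm effect size for each task with its 95% interval, as descriptive information on responsiveness and for planning. State that it does not by itself decide suitability. Judge suitability also on properties that do not depend on the course effect:

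- split-half reliability of each task's main outcome score at baseline (T0);
- stability from T0 to postintervention (T1) in the control arm, where cognitive control is not expected to improve;
- the negative-versus-neutral contrast at T0, pooled over arms;
- floor, ceiling and failed-task rates;
- task completion at each time point.

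Any numeric threshold is for the trial team to set, preferably before the between-arm task results are seen. The reliability and stability estimates should carry intervals too, since the latter will rest on about 64 control participants.

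The cost is a change of wording and a little more routine analysis. Data collection has ended, but these checks use task data already collected, and the article already plans to report missingness and completion by time point.

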#### Primary outcome: work performance

Work performance will be measured by using the 25-item Work Role Functioning Questionnaire’s (WRFQ) 57 updated version,^58^ to capture perceived difficulties in meeting work demands. Items are rated on a 5-point scale (‘difficult all the time’ to ’difficult none of the time’), with higher scores indicating better functioning. A sixth option denotes ‘does not apply to my job’. The questionnaire has not been validated in English. Validations completed in Dutch,^58^ Spanish,^59^ and Norwegian^60^ have shown good internal consistency (Cronbach alphas (α) 0.7–0.9),^58–60^ and test-retest reliability (ICC=0.66, 95% CI 0.54 to 0.76 for the total score).^58^ The WRFQ features four subscales: work scheduling and output demands (α=0.92), physical demands (α=0.92), mental and social demands (α=0.91), and flexibility demands (α=0.96).^58^ The WRFQ has been shown to possess decent convergent validity, correlating with similar measures including the Utrecht Work Engagement Scale^61^ (r=0.304),^58^ Work Ability Index^62^ (r=0.468).^58^ The primary endpoint in this trial will be the postintervention measurement. Feasibility of using the 12 week follow-up as the main outcome end-point in the later-stage trial, will be assessed. We recognise that effects at 12 weeks may not be sustained longer term. Retention at 12 weeks will help to plan the sample size for a larger trial which could also then measure outcomes longer term.

#### Secondary outcomes

##### Work-related outcomes

The participants are asked to report if they have health conditions that affect their ability to work, with options to pick one or several of the following: physical health problems, mental health problems, other health problems, no problems or prefer not to say. If a participant selects one of the first three options (ie, they have had problems), they will be asked to briefly describe these problems.

Those who self-report experiencing mental or physical health problems in the item described above will be asked to fill in the Work and Social Adjustment Scale.^63^ The scale is widely used in the National Health Service psychology services in England and has good internal consistency, α=0.82.^64^

To get a better understanding of daily fluctuations that may occur in work engagement, participants will be asked to complete a 5-item version of the Work Role Functioning Questionnaire^65^ each workday afternoon. Items are rated the same as in the full version of the questionnaire (see above).

##### Cognitive control mechanisms

Two online computerised cognitive tasks will be used to index our potential executive function mechanisms of interest. Affective cognitive control will be assessed using the Emotional Stop-Signal Task.^66^ At the beginning of each trial within the task, a negative or a neutral image appears, followed by a go-signal (left or right arrow). Participants need to respond with a corresponding key-press. On a minority of trials (20%), the go-signal is followed by a stop-signal (upwards arrow) in which a go-response is required to be inhibited. Reaction times (in both, go- and stop-trials), response accuracy (failure or success in inhibiting response) and variability in reaction time throughout the task (a proxy for the ability to overcome errors) will be measured. The main outcome of interest is the response time in stop-trials.

Participant’s ability to track dynamic changes in their environment and alter their response strategies will be measured using an affective modification of the probabilistic reversal learning task.^67^ The task will consist of six phases, three for the neutral and three for the negative condition. Each trial will begin with a negative or a neural image from the International Affective Picture System.^68^ Next, pairs of stimuli (A-B or C-D) will be presented. Participants must select a stimulus with a key-press. In each pair, one of the stimuli is more likely to be rewarded (eg, selecting A or C is reinforced on 80% of trials). Feedback is presented after each response. Through trial-and-error, participants learn which stimuli are more frequently rewarded. After a certain number of trials (a phase), the contingency of reinforcement switches. In phase 2, the other stimulus in the pair is more frequently reinforced (eg, instead of A, B is now reinforced on 80% of trials). In phase 3, the reinforcement is switched again. Reaction times and response accuracy (ie, selecting the reinforced stimulus) will be recorded. The main outcome of interest will be changes in learning performance indexed via the proportion of correct responses.

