The mechanisms underlying any effect of mindfulness on work performance are also yet to be determined while two mechanistic pathways stand out that could explain such an effect of MBPs. First, positive effects of MBPs on mental well-being are well established,^7–9^ and mental well-being is linked to better work performance.^24 25^ Conversely, mental health problems decrease employees’ performance,^26–28^ particularly if these problems are poorly managed.^29^ However, an indirect effect of MBPs on workplace performance via improved mental well-being has yet to be evaluated.

A second potential mechanism could be an improved cognitive control over mental activity, which allows one to prioritise current task-relevant goals.^30 31^ There are three potential facets of cognitive control that may be improved by MBPs: (1) shifting, that is, the ability to switch between multiple tasks; (2) updating, or the ability to frequently refresh information in working memory to ensure a currently relevant record of information and (3) inhibition: deliberately hindering dominant or automatic responses that are irrelevant to the task at hand.^32^ Improved cognitive control, in turn, may lead to better performance on workplace tasks.^11 33^

Mindfulness has been shown to have a small effect on cognitive control.^34 35^ A recent meta-analysis analysing outcomes of randomised controlled trials (RCTs) measuring the effects of cognitive control in MBPs for healthy participants found a small overall effect of Hedge’s *g*=0.2.^35^ However, we know little about how these changes in cognitive control manifest in the workplace.^13^ While mindfulness may improve performance on tasks closely related to the practice, such as counting breaths,^36^ it may not extend to other tasks, such as those completed at work.^37^

Furthermore, to date, research has primarily focused on the impact of mindfulness on cognitive control over emotionally neutral information. Yet, much of the everyday mental activity that we seek to regulate is emotionally positive or negative.^38 39^ In the two meta-analysis of MBPs’ effects on cognitive control published to date,^34 35^ only one identified study used emotional stimuli within an cognitive control task. This study reported a null-effect of meditation on cognitive control measured via an attention network test when comparing negative and neutral conditions.^40^ It is important to note that this study^40^ was likely underpowered.

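### The main stop-signal outcome, read literally, is reaction time on failed stops only, which mainly reflects go speed; it should be the estimated stop-signal reaction time

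*Protocol article*

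**What the plan says.** The protocol article (Secondary outcomes, Cognitive control mechanisms) gives the task its purpose: "Affective cognitive control will be assessed using the Emotional Stop-Signal Task". Stop-trials are described so: "On a minority of trials (20%), the go-signal is followed by a stop-signal (upwards arrow) in which a go-response is required to be inhibited". The recorded variables include "Reaction times (in both, go- and stop-trials), response accuracy (failure or success in inhibiting response", together with reaction-time variability. The section then fixes the main outcome: "The main outcome of interest is the response time in stop-trials". It mentions neither a stop-signal delay nor an estimated stopping latency.

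The facet of cognitive control at issue is defined under Background and rationale: "inhibition: deliberately hindering dominant or automatic responses that are irrelevant to the task at hand". The stop-signal task is one of two: "Two online computerised cognitive tasks will be used to index our potential executive function mechanisms of interest". The other, reversal learning, has its own main outcome, the proportion of correct responses.

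Two parts of the article use the result. Feasibility, acceptability, and procedural outcomes calls for between-condition effect sizes "For the cognitive control outcomes, to determine suitability of these measures to index mechanisms of interest". Statistical methods plans a mediation analysis of the mechanistic pathways.

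**The concern.** On a stop-trial the right behaviour is to withhold the key-press, so a successful stop produces no response time. The named outcome can be computed only from failed stops. These are the go responses fast enough to escape inhibition, a subset selected on the ability being measured. A participant who inhibits better may contribute fewer values, and one who never fails has none.

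The Objectives section expects only mindfulness to improve cognitive control and uses light exercise to separate that pathway from the mental-health pathway. If the inhibition index responds weakly or not at all to better stopping, a real effect could be missed and a suitable task judged unsuitable. Conversely, a general change in response speed could move the index with no change in inhibition. Either would mislead the design of the later trial.

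**Working it through.** **Inputs from the article.** Stop-trials are 20% of trials, the response must be withheld on them, and the main outcome is response time on them. The article gives no expected value for this outcome, so there is no figure of the plan to reproduce.

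**Inputs assumed.** Go reaction time G = Normal(450, 60) + Exponential(90) ms. Stopping latency S has a within-person SD of 30 ms, and its mean is varied. Three delay schemes were tried, because the article names none. Two further simulations with separately assumed go-time parameters are reported where marked.

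**Model (independent race).** With stop-signal delay D, a response escapes on a stop-trial when G < D + S.
- Named outcome: mean of G given G < D + S.
- Integration estimate of stopping latency: (go-time quantile at p) − mean(D), where p is the probability of responding on stop-trials.

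**Why the delay scheme decides the matter.** Tracking adjusts D until p is about 0.50, which puts D + S near the median go time whatever S is. In the simulation, mean D was 329.3 ms at S = 200 and 229.4 ms at S = 300. The sums are 529.3 and 529.4 ms. The cut-off does not move, so neither does the mean below it. With fixed delays the cut-off moves with S, and the outcome moves with it.

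**Large-sample means as mean S goes from 200 to 300 ms:**

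| Delay scheme | Named outcome (ms) | Change | p(respond) |
|---|---|---|---|
| Tracked, 50 ms steps | 473.3 → 472.9 | −0.4 | 0.50 → 0.50 |
| Four delays, 100/200/300/400 ms | 473.4 → 492.7 | +19.3 | 0.30 → 0.53 |
| One fixed delay, 250 ms | 420.6 → 474.6 | +54.0 | 0.20 → 0.60 |

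Per 80 ms these are about 0.8 × 19.3 = 15 ms for four delays and 0.8 × 54.0 = 43 ms for one.

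**Further simulations, 200 against 280 ms.**
- Tracked: 476.5 against 476.9 ms in one. In the other (exponential part 100 ms, 192 go and 48 stop trials), 475.9 against 477.3 ms, a shift of 1.4 ms against a sampling SD of about 14 ms per person. In the latter the integration estimate gave 195.5 and 274.7 ms, recovering 274.7 − 195.5 = 79.2 of the 80 ms.
- Fixed: about 23 to 24 ms with three delays and about 45 ms with one. In the three-delay run at 150/250/350 ms, the failure share changed between 26% and 47% of stop-trials.

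**Participant level.** There were 2,000 simulated participants per cell, with 200 or 400 trials (40 or 80 stop-trials) and between-person SDs of 50 ms for go time and 35 ms for latency. Correlations were:

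| Scheme | Named outcome with true latency | Named outcome with go speed | Integration estimate with true latency |
|---|---|---|---|
| Tracked | about 0.00 | 0.95–0.98 | 0.84–0.90 |
| Four delays | 0.19–0.20 | 0.89–0.94 | 0.56–0.58 |
| One fixed delay | 0.59 | 0.70–0.73 | 0.82–0.89 |

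In every scheme the named outcome follows go speed more closely than stopping latency, and the integration estimate follows latency better than the named outcome does.

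**How often the outcome is undefined.** Participants who never or always responded on stop-trials numbered 0 of 2,000 under tracking, at most 1 under four delays, and 27 (1.4%) or 16 (0.8%) under one fixed delay. Under these assumptions undefined values are rare, so the weakness is mainly one of meaning.

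**The case against.** The strongest reply is that the sentence may be shorthand for the estimated stop-signal reaction time, with the estimation method left to a fuller protocol or analysis plan. The article does not settle this. However, it lists reaction times on stop-trials among the things measured and then picks that quantity as the main outcome, which favours the literal reading. If the estimate was meant, the sentence still names the wrong quantity. The point therefore concerns a main outcome that is stated and misnamed, and does not rest on missing detail.

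A reader might go further and infer that the outcome cannot index inhibition, so that its effect size would be near zero by construction. That holds only under a tracked delay, which the article does not state; with fixed delays the measure moves. Nor do the harms all apply together. Under tracking participants fail about half their stop-trials, so few or missing values would arise only with untracked delays, where the measure does carry some information.

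A reader might also infer that the cognitive-control pathway is left without a measure. It is not: inhibition success or failure is recorded, and reversal learning has a separate outcome. Those do not remove the fault, since reversal learning is assigned to tracking change and altering strategy, and inhibition success is not the named main outcome.

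Finally, the suitability of the cognitive measures is itself a question for this feasibility trial. That lowers the severity, but a mis-scored measure cannot answer the question fairly.

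**Conclusion.** The point stands in a limited form. As written, the main stop-signal outcome is reaction time on failed stops, conditioned on failing to inhibit and driven mainly by go speed. It is essentially uninformative about stopping latency if delays are tracked to about 50% success. If delays are fixed it responds partly, by about 24 to 45 ms per 80 ms with three delays or one and about 15 ms with a wider four-delay mix, and it remains confounded with go speed and the failure rate.

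That the outcome exists only on failed stops follows from the article's own text. The sizes rest on the independent race model, assumed reaction-time parameters and an unknown delay procedure. What is exposed is the effect size and the mediation result for the inhibition facet. The Work Role Functioning Questionnaire comparison, randomisation, the reversal-learning outcome and the planned 240 participants are unaffected. Severity is moderate, because this is a secondary, exploratory outcome.

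**What to change.** Replace the sentence so that the main outcome of the task is the estimated stop-signal reaction time by the integration method, computed from go reaction times, the probability of responding on stop-trials and the mean stop-signal delay, separately for negative and neutral images. State whether the delay was tracked or fixed.

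First confirm that the delays were logged: the article does not list them among the recorded variables, and it reports data collection as finished. If they were not logged, use the recorded inhibition success rate by valence, provided delays were fixed; under tracking that rate is held near 50% by design. Use failed-stop reaction time only to check the race-model assumption.

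The cost is a wording change and a scoring script, with no further data collection and no change to the sample size, if the delays are available. The gain depends on the procedure: under mixed delays the estimate correlated only 0.56–0.58 with true latency in simulation, still well above the 0.19–0.20 of the named outcome.
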